# Neuromodulatory Effect of Sensorimotor Network Functional Connectivity of Temporal Three-Needle Therapy for Ischemic Stroke Patients with Motor Dysfunction: Study Protocol for a Randomized, Patient-Assessor Blind, Controlled, Neuroimaging Trial

**DOI:** 10.1155/2021/8820324

**Published:** 2021-01-04

## Abstract

**Background:**

The clinical efficacy of temporal three-needle therapy for stroke dysfunction has been previously demonstrated in China. However, the central mechanism of temporal three-needle therapy remains unclear. Temporal three-needle projects the sensory cortex and the motor cortex, which may impact the cortex function. Current studies seldom focus on it. Hence, according to the “scalp-cortex corresponding theory,” the underlying mechanism of temporal three-needle remains a domain for further research.

**Methods:**

This trial is designed to provide objective and visual evidence for the neuromodulatory effect and neuroimaging mechanism of temporal three-needle therapy for stroke patients. This ongoing study is a prospective, randomized, controlled, patient-assessor blind, single-center, neuroimaging trial involving two-parallel patient groups and a healthy control group. Forty eligible patients will be recruited from Shenzhen Nanshan District People's Hospital and randomized into either the experimental group or the control group. Twenty healthy volunteers will be recruited in the healthy control group and undergo baseline magnetic resonance imaging scans without any intervention. Patients in the control group will receive acupuncture at Dingnieqianxiexian (MS6), in addition to basic medicine and rehabilitative treatments. Patients in the experimental group will receive temporal three-needle therapy plus basic medicine and rehabilitative treatments 5 days per week, 10 sessions over two consecutive weeks. The primary outcome is resting-state functional connectivity, and the secondary outcomes are regional homogeneity, amplitude of low-frequency fluctuations, Fugl–Meyer assessment of the upper limb, and modified Barthel Index. All outcome measures will be assessed at baseline and after 2 weeks of intervention. *Discussion*. The results will explore the neuromodulatory effects and illustrate the central mechanism of temporal three-needle treatment from the network-level viewpoint of sensorimotor network functional plasticity and promote widespread application in real-world practice. This trial was registered at Chinese Clinical Trial Registry on 14 March 2018 with ChiCTR1800015209.

## 1. Introduction

Stroke is the second leading cause of death, and Kim et al reported that stroke remained the third-leading cause of years-of-potential-life lost worldwide [1]. The stroke incidence ranged from 76 per 100,000 population per year up to 119 per 100,000 population per year in different countries [2], and it is expected that the incidence of stroke will continue to increase as the population ages [3]. There are about two million new patients of stroke annually in China [4]. Most of the stroke survivors are associated with functional disabilities in China [5], and motor dysfunction is the most significant symptom, which results in different levels of dysfunction (including muscle atrophy, joint stiffness, shoulder pain, deep vein thrombosis of the lower limb, long-term brakes, infection, anxiety, and depression) and disability in daily life. The stroke impact in China is more severe compared to the worldwide average levels. DALYs (disability adjusted life-years) caused by stroke rank 3rd in global epidemiologic study and first in China [6]. Overall poststroke care costs were the highest in the USA ($4850/per patient month) [7], which indicates that stroke not only brings pain to patients themselves but also imposes a great financial burden on families and communities in most countries, which has become a critical public health problem.

In 2002, the World Health Organization recommended acupuncture as a therapy for stroke [8]. Temporal three-needle acupuncture is one of Jin's three-needle therapy systems created by [name] in China. The temporal I needle is located on the hairline 2 cun above the apex of the ear; the temporal II needle and the temporal III needle are located 1 cun from the temporal I needle on either side in the horizontal direction [9]. Temporal three-needle therapy integrates the meridian acupoint theory in Chinese traditional medicine, modern neurological theory, and anatomical rationale [10, 11]. The location of the temporal three-needle is highly overlapped with the temporal bone seams, which is a crevice left by the congenital development process [12]. Additionally, the nerve is extended into the skull through the gap of the skull, which can effectively mobilize the neuron activity after acupuncture, and the position of the temporal three-needle ranged including the precentral gyrus and postcentral gyrus could widely affect the motor and sensory areas [13]. Meanwhile, the bioelectric effect of acupuncture at the location can be transmitted to the cerebral cortex, which can quickly rebuild the function of injured neurons in the functional area and strengthen the compensatory ability of the brain [11]. Moreover, the temporal bone is much thinner than other skulls, and its suture is mostly densest; acupuncture sensation is easier to be conducted, and the acupuncture effect is better. As a result, the acupoint selection of temporal three-needle has a certain representative. In real-world clinical practice, acupuncture on the left temporal three-needle treats right limb paralysis and acupuncture on the right temporal three-needle for the left paralysis, which is widely used in the poststroke rehabilitation in China [11, 14–18], especially motor dysfunction [14, 15, 19].

Because the study design is a superiority trial and stroke patients conventionally receive acupuncture at the scalp acupoint in current clinical practice in China, placebo (sham) stimulation or a blank control may violate the patient willingness. This trial will choose Dingnieqianxiexian (MS6) in the International Standardization Scheme for Scalp Acupuncture Points as the positive comparator in the control group. MS6 is an international standardized scalp acupoint, which refers to a diagonal line from Qianshencong (EX-HN1) to Xuanli (GB6) [20], and is projected to the precentral gyrus [21]; it is responsible for the autonomous movement of the limbs [20]. Studies have indicated that, on the basis of body acupuncture, temporal three-needle therapy is superior to acupuncture at MS6 with respect to daily life activities [22], motor function [22], and motor-related sensory disturbances [19].

However, the central mechanism of temporal three-needle therapy on stroke recovery remains unclear, especially in neuroimaging. From the last several years, with the rapid development of medical imaging technology, magnetic resonance imaging (MRI) has gradually become one of the main methods for studying the mechanism of acupuncture. Resting-state fMRI (rs-fMRI) only requires the subjects to stay still and close their eyes while scanning and keep their body as immobile as possible without thinking about anything. Rs-fMRI reflects intrinsic functional patterns and the spontaneous activity of the brain's cortex [23], which is a useful technique for studying the mechanism of acupuncture [24]. In this trial, we plan to apply rs-fMRI to explore the central mechanism of temporal three-needle treatment.

Previous neuroimaging studies demonstrated that motor disorders in stroke patients were associated with functional connectivity (FC) abnormalities in the sensorimotor network or sensorimotor cortex [25, 26]. Moreover, functional recovery after stroke is associated with preserved FC of motor to nonmotor networks [27]. Acupuncture can increase the default mode network and sensorimotor network functional connectivity with pain-, affective-, and memory-related brain areas compared with sham acupuncture [24]. Several studies have also shown that acupuncture increases the sensorimotor network connectivity with pain-related brain regions in healthy adults or inhibits neuroinflammation in the sensorimotor cortex after ischemic stroke [28, 29]. However, the neuroimaging mechanism based on temporal three-needle therapy in hemiplegic patients with stroke remains unclear. The theoretical basis of scalp acupuncture is mainly based on the two aspects [20]: (1) the traditional Zangfu meridians theory and (2) scalp-cortex corresponding theory. According to the “scalp-cortex corresponding theory,” the temporal three-needle projects the cortex of the sensory area and the motor area on the temporal ear, and the bioelectric effect produced by acupuncture in this area is transmitted to the cerebral cortex, which can impact the function of the cerebral cortex [11]. Given the abovementioned viewpoints, we hypothesize that the underlying neuroimaging mechanism on neuromodulatory effects in temporal three-needle acupuncture may be related to sensorimotor network functional connectivity.

Therefore, our first objective is to assess the neuromodulatory effect of temporal three-needle therapy on resting-state regional brain activity, whole-brain activity, and motor function. Our second objective is to explore the relationship between alterations in functional connectivity at the sensorimotor network level and changes in behavioral performances to demonstrate the underlying neuroimaging mechanism of temporal three-needle treatment.

## 2. Methods

### 2.1. Study Design and Setting

This study will be a two-week, prospective, randomized, patient-assessor blind, controlled, single-center, superiority, neuroimaging trial with two-parallel patient groups and a healthy control group. This study will take place mainly in Shenzhen Nanshan District People's Hospital, Shenzhen, Guangdong Province, China. In this trial, we will recruit subjects into two categories. The first category will comprise healthy controls, and the second will comprise patient subjects. A total of 20 age-, gender-, and education-matched healthy subjects will be recruited into the healthy control group. The purpose of healthy control recruitment is to establish a baseline normal MRI data set to facilitate comparison with the MRI data of the patients' groups. The healthy control group will receive baseline MRI scans without any intervention. Forty eligible patients will be randomized into two groups: (1) the experimental group and (2) the control group, with a 1 : 1 allocation ratio. All patients will take medicine for secondary prevention of stroke (e.g., antihypertensive, hypoglycemic, antiplatelet, and hypolipidemic drugs) and conventional rehabilitative treatments according to the Chinese stroke rehabilitation treatment guidelines [5] (e.g., physical therapy (PT) and occupational therapy (OT)); these treatments will be consistent across the patient groups. In the control group, patients will receive acupuncture at MS6 following basic drug treatments and conventional rehabilitative treatments. Patients in the experimental group will receive temporal three-needle acupuncture 5 days per week, 10 sessions over 2 consecutive weeks, plus basic drug treatments and conventional rehabilitative treatments. Acupuncturists with at least 10 years of clinical experience will perform acupuncture therapy (including temporal three-needle therapy and MS6 therapy). Professional rehabilitative therapists with above 5 years of clinical experience will conduct conventional rehabilitative treatments (PT and OT) for the patients.

The planned flowchart of the trial is shown in Figure 1. The timeline for assessment is provided in Table 1. This study protocol is in compliance with the requirements of the Helsinki Declaration. Ethical approval was provided by the Ethics Committee of Shenzhen Nanshan District People's Hospital in February 2018. In addition, Shenzhen Nanshan District People's Hospital is also carrying out this trial and is responsible for the coordination of all departments' activities (e.g., study protocol registry, staff training, informed consent implementation, and data management). This protocol follows Standard Protocol Item: Recommendations for Interventional Trials (SPIRIT) 2013 [30] (see Additional File 1 in Supplementary Materials available here) and the Consolidated Standards of Reporting Trials (CONSORT) 2010 statement for nonpharmacological interventions [31].

### 2.2. Sample Size Calculation

Our primary outcome will be resting-state FC measured by rs-fMRI. Because millions of voxels are used to indirectly estimate the blood oxygen level-dependent (BOLD) signal and traditional power calculations are of no significance [32], we calculated the sample size according to the relevant published articles. Previous rs-fMRI study of the acupuncture mechanisms in stroke had a sample size of 20 cases for the healthy control group [33]. Moreover, a study on the effects of sample size on cerebral response to acupuncture with fMRI had shown that the imaging results in 17 healthy controls were similar to the results of studies with 21 cases [34], which may suggest that approximately 20 subjects maybe a relatively common choice in rs-fMRI studies after acupuncture. The sample size in acupuncture mechanism study using rs-fMRI with stroke patients typically ranges from a few cases to approximately 20 cases [33, 35–37]. Because this trial is a neuroimaging study, the primary outcome will be based on the subjects' MRI image processing, and patients with left cerebral ischemia accompanied by right limb hemiplegia will be enrolled in this study so as to ensure the relative consistency of cerebral ischemia lesions and reveal the neuroimaging mechanism more regularly.

Under the condition of left brain ischemia stroke with right limb hemiplegia in this study, we plan to enroll 20 patients diagnosed with ischemia stroke in each patient group (20 in the experimental group and 20 in the control group) and 20 healthy volunteers in the healthy control group.

### 2.3. Participants and Recruitment

Forty patients diagnosed with stroke will be recruited from Shenzhen Nanshan District People's Hospital. Three trial staff will conduct the recruitment in accordance with the inclusion and exclusion criteria to determine whether the patients are eligible for the study. Patients will be recruited through oral recruitment during daily consultation, advertisements, WeChat in Shenzhen, and volunteer recommendations. All patients' subjects will undergo a baseline evaluation, including complete the collection of demographic and clinical data.

After completion of the recruitment of the forty patients, a total of 20 age-, gender-, and education-matched healthy subjects will be recruited from the community-dwelling population in the Nanshan District in Shenzhen, Guangdong Province, China, according to the demographic characteristics of the experimental group. The recruitment methods will be the same as that of the patients.

Additionally, all patients and healthy controls will be invited to voluntarily sign the informed consent form.

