#### 2.4.1. Inclusion Criteria

The inclusion criteria for patients with stroke are as follows: (1) diagnosis of ischemic stroke confirmed by brain CT or MRI; (2) left cerebral ischemia (including the stroke patients with anterior and posterior circulation infarction) with right limb hemiplegia; (3) first-ever clinical stroke occurring between 2 weeks and six months; (4) aged between 30 and 70 years; (5) stable medical condition, Brunnstrom stages I–V; and (6) written informed consent to participate.

The inclusion criteria for healthy controls include the following: (1) can be matched to the patient's age, gender, and education; (2) has no acupuncture treatment in the last month; (3) has no history of head trauma, psychiatric disease, neurological disease, or physical activity disorder; (4) has no MRI contradictions; and (5) has provided written informed consent.

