### 2.5. Randomization and Allocation

After meeting the selection criteria, 40 eligible patients will be randomly assigned into either the experimental group or the control group at an allocation ratio of 1 : 1 after signing written informed consent forms. The random sequence will be created by a third-party professional statistician of Shenzhen University using STATA 12.0 software (StataCorp, Texas, USA). The randomization list will only be seen by this research coordinator and will be concealed from other study personnel. Participant assignments will be hidden using sequentially numbered, opaque, sealed envelopes. The research coordinator that assigns the groups will not participate in the patients' inclusion, the subsequent trial process, or the assessment of results.

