### 2.6. Blinding

The trial will be conducted using a patient-assessor blind design. The patients, assessors, and statisticians will not be aware of which group the patients are in. They will only be told whether data will belong to group A or group B, but they will not be aware of which group is the experimental group or the control group. Furthermore, they will not even know whether the trial is designed to be a noninferiority trial, an equivalent trial, or a superiority trial, thus avoiding human factors affecting the results of the data analysis.

Regarding acupuncture implementation, acupuncture doctors cannot be blinded, so unblinded acupuncture doctors will apply the acupuncture intervention depending on the patients' intervention arm.

The blind method will be applied throughout the whole study process. A member of the trial staff will supervise the process of blind implementation and will disclose the blind code after the statistical analysis is completed. Unblinding will be considered only in a critical medical emergency.

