Studies have found that abnormal brain structures and functions exist in patients after stroke compared with age- and gender-matched healthy controls [53, 54]. In this trial, we will aim to investigate the neuromodulatory effect of sensorimotor network FC of temporal three-needle therapy for ischemic stroke patients with motor dysfunction. First, we will compare the differences in baseline rs-fMRI metrics between the healthy subjects and the stroke patients to confirm the difference between the healthy subjects and stroke patients. Second, to determine the difference due to the temporal three-needle treatment, we will compare the changes in the rs-fMRI metrics between the experimental group and the control group to demonstrate whether motor function alteration is related to brain functional neuroplastic changes after temporal three-needle treatment. Although a large number of studies on the use of temporal three-needle therapy for the treatment of motor dysfunction, speech disorders, dysphagia, and depression after stroke have indicated clinical behavioral effects [11, 14–18], to the best of our knowledge, our study will be the first randomized neuroimaging trial with both a positive control group and a healthy control group to examine the actual effects by means of rs-fMRI.

This study has several strengths. First, the implementation of rigorous randomized, patient-assessor blind, controlled, neuroimaging trial will provide visual and objective evidence about how temporal three-needle treatment improves motor dysfunction in ischemic stroke patients. Second, the combined assessments of rs-fMRI and behavioral data will be used to identify the neuromodulatory effects of temporal three-needle therapy in stroke patients. Third, research based on the FC within the sensorimotor network, and between the sensorimotor network and nonmotor network, is better for understanding the mechanism of temporal three-needle therapy in stroke according to the “scalp-cortex corresponding theory.”

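### Healthy controls are matched to the experimental arm only, which needs allocation information before the analysis and leaves the reference group matched to 20 of the 40 patients it serves

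*Protocol article*

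**What the plan says.** Section 2.3 of the protocol article sets both the order and the target of matching. On order: "After completion of the recruitment of the forty patients, a total of 20 age-, gender-, and education-matched healthy subjects will be recruited". On target, the same sentence matches them "according to the demographic characteristics of the experimental group".

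Other sections describe the healthy group differently:
- Section 2.1 gives its purpose as to "establish a baseline normal MRI data set to facilitate comparison with the MRI data of the patients' groups", with groups in the plural.
- Section 2.4.1 requires only that a healthy volunteer "can be matched to the patient's age, gender, and education", with no arm named.
- Section 3 states the planned contrast: "we will compare the differences in baseline rs-fMRI metrics between the healthy subjects and the stroke patients".

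On access to the allocation, section 2.5 says: "The randomization list will only be seen by this research coordinator and will be concealed from other study personnel". It also keeps that coordinator out of patient inclusion, the later conduct of the trial and outcome assessment. Section 2.6 gives patients, assessors and statisticians only the labels A and B, and says that a staff member "will disclose the blind code after the statistical analysis is completed". The acupuncturists are the only other people described as knowing the allocation, and they have no stated part in selecting healthy controls.

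**The concern.** Two things do not fit together.

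First, to match on one arm, someone has to separate the 20 experimental patients from the 20 MS6 patients. The healthy scans feed the imaging analysis in section 2.11.1, so this happens before the analysis is complete. The concealment and blinding rules leave nobody in a position to do it. If the matching is close, the demographic table itself may also show the statistician which label is experimental. The primary outcome is an imaging measure that the analyst processes by a data-driven method, so analyst blinding has real value here.

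Second, the healthy group is meant as a normal reference for the stroke patients, but it is tied to half of them. A chance difference between the arms in age, gender or education then carries over into the healthy-versus-stroke baseline contrast on FC, ReHo and ALFF, although the matching could avoid it.

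**Working it through.** **Inputs.** Group sizes are 20 experimental, 20 control and 20 healthy (section 2.2), with 1:1 allocation (section 2.1). The sizes come from published studies, not from a power formula, so the only figure to reproduce is the sum 20 + 20 + 20 = 60, which agrees. The article gives no SD for any matching variable. An age SD of 8 to 12 years is assumed below.

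**Step 1: can the rule be carried out as written?** Setting the sections side by side:

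| Section | What it implies |
|---|---|
| 2.3 | Selection of healthy controls needs the experimental arm's profile |
| 2.5 | Only the coordinator sees the list, and takes no part in what follows |
| 2.6 | Code disclosed after the analysis |
| 2.11.1 | The analysis uses the healthy group's data |

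The profile is needed before the analysis, and no one is named who may supply it. The rules conflict.

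**Step 2: size of the mismatch.** Suppose the healthy group reproduces the experimental arm's covariate mean exactly. In units of the covariate's SD:
- Against the MS6 arm, the SD of the chance difference is sqrt(1/20 + 1/20) = sqrt(2/20) = 0.316.
- The pooled mean is the average of the two arm means, so experimental minus pooled is half the arm difference: 0.316 / 2 = 0.158.

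The expectation of both differences is zero under randomisation. By the normal approximation:

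| Difference exceeds | versus MS6 arm | versus all 40 |
|---|---|---|
| 0.25 SD | 43% | 11% |
| 0.5 SD | 11% | 0.2% |

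In years of age:
- Against all 40: 0.158 × 8 = 1.3 and 0.158 × 12 = 1.9.
- Against the MS6 arm: 0.316 × 8 = 2.5 and 0.316 × 12 = 3.8.
- The corresponding 95% ranges (1.96 times the unrounded SD) are ±2.5 to ±3.7 years and ±5.0 to ±7.4 years.

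For sex, the hypergeometric probability that the arms differ by 20 percentage points or more is 30% to 34%, assuming that 50% to 70% of the patients are male.

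**Step 3: could the A/B labels leak?** A simulation assumed mean age 58 years, SD 10 with values limited to 30 to 70, and 65% male. Each healthy subject was individually matched to an experimental patient, exactly on sex and on age within a tolerance. The label whose mean age and sex share lay closer to the healthy group was then picked. The pick was correct in 99.9% of trials with exact age matching, 99.0% within 2 years, 98.6% within 3 years and 97.5% within 5 years. These figures depend on tight individual matching, which the article does not specify. Matching only to a group profile would leak less.

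**Step 4: effect of pooling.** If the target is all 40 patients, the by-design mismatch with the pooled patients goes from 0.158 to 0. The mismatch with the MS6 arm falls from 0.316 to 0.158, and that with the experimental arm rises from 0 to 0.158. No allocation information is used.

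**The case against.** The strongest reply is that the healthy group plays no part in the primary decision. Section 2.11.2 bases superiority on experimental versus control, and the healthy subjects have one baseline scan for a supporting contrast. That stands: mis-targeted matching cannot bias the randomised comparison, and only a label leak could touch it.

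Second, an aggregate profile of the experimental arm (age distribution, sex ratio, education) would satisfy section 2.3 without identifying any patient, and the acupuncturists already know the allocation. This also stands in part. A reader might infer that recruiters must learn all 40 allocations; the text does not support that. The profile would still be allocation information, however, and the article names no one who may release it under sections 2.5 and 2.6.

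Third, a reader might infer that outcome assessors or patients are unblinded. Nothing shows this. Table 1 limits FMA and MBI to the patient groups, no section has assessors selecting or seeing healthy subjects, and matching starts only after the last patient is recruited.

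Fourth, a reader might see a built-in age or sex bias, or confounding of disease status with scan date. The imbalance has expectation zero, and against all 40 patients it is modest. On scan date, section 2.9 puts all scans on one scanner and the article documents no drift. Recruiting controls after the patients is also what allows matching to a known profile.

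**Conclusion.** The point holds as an internal conflict of moderate severity. The matching rule in section 2.3 needs allocation information before the analysis, which sections 2.5 and 2.6 do not allow. It also ties to one arm a reference group that sections 2.1, 2.4.1 and 3 relate to the patients in general.

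The mismatch is chance imbalance, with an SD of 0.158 of a covariate's SD against the pooled patients and 0.316 against the MS6 arm. These figures assume perfect matching on means; the figures in years also rest on the assumed age SD. The label leak is a possibility whose strength depends on the unstated tightness of matching. The consequence for the randomised comparison is limited to possible loss of statistician blinding. The documents do not support any claim that assessors or patients would be unblinded, or that every patient's allocation would be revealed.

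**What to change.** Change the matching clause in section 2.3 to: *frequency-matched on age, gender and education to all 40 randomised patients pooled, without reference to allocation*. Keep the 20 healthy controls and the stated recruitment order. Baseline demographic data are collected on every patient, so the pooled profile is available without opening the code. Section 2.3 would then agree with sections 2.1, 2.4.1, 2.5, 2.6 and 3.

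The cost is one sentence, with no extra volunteers or scans, provided that the change is made before any healthy control is selected. Section 2.14 reports the trial as still recruiting, but does not say whether healthy subjects are among those enrolled. The downside is slightly looser matching to the experimental arm taken alone.
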